### Eligibility criteria {10}

The following are the inclusion criteria:Aim 1: Clinicians (physicians, nurse practitioners, physician assistants), nurses, CPs, administrators, case managers, social workers, and other stakeholders likely to be engaged in or impacted by the CACP programAim 2: Adults (age ≥ 18 years) who are (1) currently admitted to the ED or hospital or (2) in a pre-hospital (i.e., outpatient) setting but being considered for referral to the ED or hospital and who do not require hospital-level monitoring or care other than services that could be delivered by CPs in the ambulatory setting if such services were available to themAim 3: Patients enrolled in the CACP program, CPs affiliated with the CACP program, health care team members (clinicians, case managers, social workers) who referred participants enrolled in the CACP intervention arm, and administrators involved with the CACP program or affiliated programs and services

The following are the exclusion criteria:Aim 1: No exclusion criteria.Aim 2: Patients will be excluded if (1) the referring clinician believes they require ED or hospital care; (2) they or their legal guardian/representative are unable or unwilling to give written informed consent; (3) they demonstrate clinical, behavioral, or cognitive instability, as determined by the referring clinician or the CACP service; (4) their living conditions are deemed unsafe for CPs to enter (e.g., the patient refuses to secure weapons or animals prior to CP arrival); (5) they were enrolled in the trial during an earlier hospitalization or ED visit; or (6) they are requesting services in a location outside the CACP service area or in a skilled nursing facility (SNF). The referring service completes a checklist prior to referring patients to the CACP program (available as a system smart phrase within the EHR) that explains these criteria, including patient confirmation of factors related to the safety of CPs conducting home visits. Patients can only be enrolled in the trial if the CACP program has the census capacity to accept new patients.Aim 3: There are no exclusion criteria for clinicians or other clinical or administrative stakeholders. Patient participants will be excluded from recruitment to interviews if they (1) have a communication barrier due to medical illness or cognitive impairment or (2) are seriously ill or hospitalized at the time of interview recruitment.

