#### Intervention description {11a}

The CACP program is an extension of an established care delivery model offered by the Mayo Clinic Ambulance Service. In the CACP program, the referring clinician identifies services or interventions clinically required for the patient. This may include patient education, clinical reassessment, laboratory specimen collection, medication administration, wound care, and other services within the CP scope of service. Visits are limited to up to two per day and are generally no more than 2 h in duration. The referring service or the patient’s primary care provider (PCP) or another ambulatory care provider, as appropriate, oversees clinical care with the support of the CP medical director. CPs will communicate with the referring service and/or their medical director as appropriate (usually after every visit but individualized based on the patient’s need and instructions provided by the referring service) via EHR inbox messages, the EHR chat function, or telephone. Patients will graduate from the program once the goals outlined in the referral are completed. Upon graduation, the CP team will communicate directly with a clinician assuming the patient’s care (e.g., PCP).

The CACP program will be available to patients at no cost, and services provided by CPs under this trial will not be submitted to participating patients’ insurance. If CPs facilitate or assist with a service performed by other members of the health care system, the services performed by others will be processed by the patient’s insurance as per usual procedures. For example, if a patient is seen for clinical assessment, venipuncture with laboratory sample collection, and administration of intravenous fluids, the assessment, venipuncture, IV start, and IV fluids themselves will be free to the patient. However, the analysis of the blood sample conducted by a clinical laboratory after it is collected and delivered by CPs will be processed through insurance. In contrast, point-of-care testing performed by CPs will be at no cost to the patient.

Participants randomized to usual care will be treated without consideration of CP care options. We anticipate that most will be referred to the ED and admitted to the hospital or have alternative care pathways (e.g., home health agency, SNF, frequent clinic visits) to meet their clinical needs. The start time for both cohorts will be the day after randomization.

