### Outcomes {12}

Trial outcomes for the three specific aims are detailed in Tables 1 and 2. Aim 1 is a formative evaluation of the implementation context that seeks to rapidly identify and address anticipated barriers and challenges, as well as identify opportunities that could impact the successful implementation of the pragmatic trial and the CACP program. It involves qualitative interviews with CPs, clinicians and other members of the health care team, and administrators, in the 3-month period directly before trial enrollment commences with anticipated qualitative outcomes related to acceptability and feasibility, as well as detailed recommendations for targeted actions.

**Table 1 Tab1:** Elements of primary and secondary outcomes

Domain	Specific measurement	Specific metric	Method of aggregation	Time point
Potential barriers to CACP implementation (aim 1)	Qualitative interviews	Perspectives on acceptability, feasibility, and workflow impact	Content analysis by construct by role, e.g., CP, clinician, administrator	Prior to the start of the enrollment period (− *T*_1_)
CACP effectiveness (aim 2 primary)	EHR review	Days alive out of ED or hospital 0 and *T*_3_	The number of days the patient was alive and out of the ED or hospital (not in hospital, excluding planned hospital admissions for scheduled surgeries, procedures, and/or treatments) between 0 and *T*_3_	Comparison between the groups will be made at *T*_3_
CACP effectiveness (aim 2 secondary)	EHR review	Unplanned ED visits, hospitalizations, or death (composite endpoint and individual)	The number of events per participant per 30 days, the percent of participants with events within 30 days, and time to event(s). Will report as a composite outcome and individually	Comparison between the groups at *T*_4_ and *T*_5_
CACP effectiveness (aim 2 exploratory)	EHR review	SNF care	The percent of participants admitted to SNF within 30 days of randomization and duration of SNF stay	Comparison between the groups will be made at *T*_3_
CACP safety (aim 2 secondary)	EHR review	Unplanned hospitalizations, ED visits, falls with injury, medication errors with harm, and death	The percentage of patients with events within 30 days, the total number of events within 30 days, and time to event(s). Will report as a composite outcome and each outcome individually	Comparison between the groups at *T*_3_ and the day after randomization to *T*_3_

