Aim 2 will evaluate CACP effectiveness (compared to usual care) and implementation outcomes using mixed methods. The primary effectiveness outcome is the number of days alive out of ED or hospital within 30 days of the day following randomization, ascertained by EHR review; this outcome includes all unplanned hospitalizations, ED visits, and deaths, which will also be assessed separately as safety endpoints. This primary outcome measure was selected for its relevance to the desired goal of the CACP program, i.e., shortening and/or preventing ED and hospital utilization. It captures both the initial impact of CP services availability and the effectiveness of the program in meeting the needs of the patient and preventing the return to the ED/hospital subsequent to initial discharge. Planned hospital stays will be excluded from the primary outcome. The secondary outcomes include the proportions of patients experiencing the components of the primary outcome (i.e., percent of patients with unplanned hospitalizations, ED visits, and death), the rates of each component of the primary outcome, the proportion of patients requiring SNF care, as well as patient-reported health-related quality of life (HRQoL) and treatment burden using the patient-reported EQ-5D [19] and PETS [20] measures. For patients in the CACP program, patient satisfaction will also be evaluated. Implementation outcomes, organized by the RE-AIM implementation evaluation framework (Reach, Effectiveness, Adoption, Implementation, and Maintenance), as shown in Table 2, will be ascertained using administrative and EHR data and interviews. Reach and adoption outcomes include metrics for the eligible population, while other implementation outcomes are specific to the intervention group. Additional secondary analyses will assess for the heterogeneity of treatment effects as a function of baseline ED/hospital utilization, source of referral, reason for referral, services delivered, patient demographics (age, sex, rurality, race/ethnicity, limited English proficiency, area-level deprivation), number of CP visits, and duration of CP care. Sensitivity analyses will be performed excluding hospice deaths and utilizing the per-protocol rather than the intention-to-treat approach.

Aim 3 will assess acceptability/satisfaction and perceived sustainability using surveys [21] and interviews with patients, CPs, clinicians and other members of the health care team, and administrators.

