#### Participant timeline {13}

The schedule of enrollment, intervention, and assessment for patient participants is shown in Table 3. Adults (age ≥ 18 years) being treated in the pre-hospital environment (e.g., outpatient clinic or home), ED, or hospital will be identified by their treating clinicians as needing and being clinically appropriate for outpatient management with supportive services provided by the CP team. Clinicians will query patient interest, and a member of the study team will subsequently approach, consent, and enroll patients. Subsequent to consent, they will be randomized 1:1 to CACP versus continued usual care, with stratification by source of referral (pre-hospital versus ED versus hospital) and location (Minnesota versus Wisconsin, corresponding to the two different CP teams delivering the intervention). Participants randomized to CACP will be eligible to receive CP services as ordered by the referring clinician. Participants randomized to usual care will continue to receive care as they would otherwise, including being referred to the ED (for patients in the pre-hospital setting), admitted to the hospital (for patients in the ED), or remain in the hospital (for patients already in the hospital) as appropriate.

**Table 3 Tab3:** Flow of study procedures for patient participants

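### The secondary and safety event endpoints do not separate the index stay or visit from later events, although the index pathway differs by arm by design

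*Protocol article*

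**What the plan says.** Eligibility criteria {10} admits patients who are "currently admitted to the ED or hospital" as well as outpatients being considered for referral. Randomization is stratified by three referral sources and two locations, giving six strata (Implementation {16c}). ED and hospital referrals are two of the three sources, hence four of the six strata.

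Under usual care, outpatients may be sent to the ED, ED patients may be admitted, and inpatients "remain in the hospital (for patients already in the hospital) as appropriate" (Participant timeline {13}).

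Outcomes {12} names as secondary endpoints "the proportions of patients experiencing the components of the primary outcome (i.e., percent of patients with unplanned hospitalizations, ED visits, and death". In Table 1 the effectiveness row is "Unplanned ED visits, hospitalizations, or death (composite endpoint and individual", summarized by the number of events, "the percent of participants with events within 30 days, and time to event(s". The safety row covers the same ED visits, hospitalizations and deaths, plus falls with injury and medication errors with harm, as "The percentage of patients with events within 30 days, the total number of events within 30 days, and time to event(s".

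Two rules bear on what counts. Planned admissions are excluded, and Intervention description {11a} sets the clock: "The start time for both cohorts will be the day after randomization".

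**The concern.** Neither rule settles how to score an acute stay that is still running when the clock starts, or an admission out of the ED visit in which the patient was randomized. An acute index stay is not a planned admission, and a start date does not say whether an episode that straddles it is an event.

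Outcomes {12} points both ways. It calls these endpoints components of the primary outcome, and says of the primary outcome that "It captures both the initial impact of CP services availability and the effectiveness of the program in meeting the needs of the patient"; on that reading the index stay counts. The same sentence goes on to name keeping patients from coming back after they have first been discharged; on that reading only returns count.

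The choice is not neutral between arms. CACP aims to get ED and hospital patients home sooner, while usual care admits or keeps them. If the index episode counts, the percentage largely measures the allocated pathway. If only later events count, it measures whether care failed afterwards. One pooled percentage, used for both effectiveness and safety, cannot tell the two apart. In the safety composite the inclusive rule loads events onto usual care and could conceal harm under CACP.

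**Working it through.** **The plan's own figures.** The protocol states no event rate or power for these endpoints. Its 120 per group belongs to the primary outcome (2 days, SD 5, two-sided 0.05, 80% power). Those inputs give 2 × (1.96 + 0.84)² × 5² / 2² ≈ 98, or 99 per group with the t-test, but that does not bear on this point. Here 120 per arm serves only as a denominator.

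**Assumptions (none from the protocol).**
- s: share of patients already in the ED or hospital at randomization; 1/3 to 0.8.
- r: 30-day risk of a new event, set equal in both arms; 20% or 30%.
- q: share of those s patients still in, or admitted from, the index episode on day 1; CACP versus usual care 10/50%, 20/80% or 30/50%.
- Index status and later events are independent.

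**Rule A, later events only.** Risk = r in each arm. With r = 20%: 24/120 versus 24/120, difference 0. The zero follows from setting r equal.

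**Rule B, index episode counted if present on day 1.** Risk = r + (1 − r) × s × q. Central case, s = 2/3 and r = 0.20:
- CACP: 0.20 + 0.80 × 2/3 × 0.10 = 0.253 (30/120)
- Usual care: 0.20 + 0.80 × 2/3 × 0.50 = 0.467 (56/120)
- Difference 21 points; Pearson chi-square (the planned test) p = 0.0005

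Selected cases under Rule B:

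| s | r | q, CACP / usual care | CACP | Usual care | Difference | p |
|---|---|---|---|---|---|---|
| 1/3 | 30% | 30% / 50% | 37.0% | 41.7% | 5 points | 0.43 |
| 2/3 | 20% | 30% / 50% | 36.0% | 46.7% | 11 points | 0.09 |
| 0.8 | 20% | 30% / 50% | 39.2% | 52.0% | 13 points | 0.05 |
| 2/3 | 20% | 10% / 50% | 25.3% | 46.7% | 21 points | 0.0005 |
| 0.8 | 20% | 20% / 80% | 32.8% | 71.2% | 38 points | <0.0001 |

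The first and last rows are the extremes of the grid. If every patient in the ED or hospital at randomization were scored as an event in both arms, the central case would give 0.20 + 0.80 × 2/3 = 73% in each arm, again no difference.

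**Masking of harm.** Let the true later-event risk be 30% under CACP and 20% under usual care, with s = 2/3.
- q = 10/50%: CACP 0.30 + 0.70 × 2/3 × 0.10 = 0.347; usual care 0.467. A true 10-point excess appears as a 12-point benefit.
- q = 30/50%: CACP 0.30 + 0.70 × 2/3 × 0.30 = 0.440; usual care 0.467. The excess appears as a 3-point benefit.
- q = 30/50% with s = 1/3: CACP 0.370; usual care 0.333. The excess shrinks from 10 to 4 points.

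**Time at risk under a later-events rule.** If the window ends 30 days after randomization, the arm with the longer index stay is observed for less time after discharge. At a constant hazard giving 20% over 30 days, four extra index days give 1 − 0.80^(26/30) = 17.6%, which slightly favours usual care.

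**The case against.** The strongest reply is that this is event-counting detail for secondary endpoints, which a condensed article may leave to the full protocol or analysis plan. There are also anchors: the clock starts the day after randomization in both arms, and the section on discontinuing interventions {11b} speaks of care needed after randomization. These lean towards new encounters, and effect heterogeneity by referral source is already planned. The lean is real, but it leaves the ongoing stay and the admission from the index ED visit unscored. The point also goes beyond omitted detail, because Outcomes {12} itself supports two opposing readings.

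Four stronger readings are tempting, and the documents do not support them.
- *The trial's data will show a large benefit or none depending on the rule.* The zero comes from assuming equal new-event rates, and the size of the shift depends on the assumed contrast. At 30% versus 50% it is 5 to 13 points with p above 0.05.
- *Every referral source is affected alike.* A pre-hospital patient is in no stay at randomization, and avoiding an ED visit or admission is what the program is for. Those events should not be defined away.
- *The primary outcome is compromised.* Days in hospital from day 1 simply do not count as days out, whichever episode they belong to.
- *The accrual pause rule is shown to be distorted.* Serious events are defined by what they result in, and an adjudication committee blinded to allocation (though with access to the record) reviews them. Both point towards new events.

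**Conclusion.** The concern holds for the percent, number and time-to-event endpoints built on unplanned ED visits and hospitalizations, for ED and hospital referrals. The protocol does not say whether the index episode is an event, its text supports both an inclusive and a returns-only reading, and the index pathway differs by arm by design. With equal new-event rates assumed, the scoring rule alone moves the arm difference from 0 to between about 5 and 38 points. The inclusive rule can shrink or reverse a true excess of later events under CACP. All rates are assumptions, so the figures show how sensitive the endpoints are to the rule and do not predict the result. The change should be made, since the same events serve as the safety composite.

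**What to change.** Replace the single pooled definition in Table 1 with two outcomes.

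1. **Index episode.** Remaining index length of stay for ED and hospital referrals; admission from the index ED visit for ED referrals; ED visit or admission for pre-hospital referrals.
2. **Subsequent unplanned ED visits or hospitalizations**, used for the safety composite. For ED and hospital referrals, count encounters that begin after discharge from the index episode. For pre-hospital referrals, state explicitly when the index referral ends, so that an early ED visit or admission under CACP is not dropped.

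State the time origin for time to event. Handle unequal time at risk, for example by reporting events per day at risk, or events over a fixed 30 days from index discharge, next to the 30 days from randomization. Report both outcomes by referral source as well as pooled.

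The cost is a revised definition and some extra tabulation from EHR admission and discharge times. Pooled event rates will be lower than under the inclusive rule, and some difference in time at risk between arms will remain.

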#### Participant timeline {13}

The schedule of enrollment, intervention, and assessment for patient participants is shown in Table 3. Adults (age ≥ 18 years) being treated in the pre-hospital environment (e.g., outpatient clinic or home), ED, or hospital will be identified by their treating clinicians as needing and being clinically appropriate for outpatient management with supportive services provided by the CP team. Clinicians will query patient interest, and a member of the study team will subsequently approach, consent, and enroll patients. Subsequent to consent, they will be randomized 1:1 to CACP versus continued usual care, with stratification by source of referral (pre-hospital versus ED versus hospital) and location (Minnesota versus Wisconsin, corresponding to the two different CP teams delivering the intervention). Participants randomized to CACP will be eligible to receive CP services as ordered by the referring clinician. Participants randomized to usual care will continue to receive care as they would otherwise, including being referred to the ED (for patients in the pre-hospital setting), admitted to the hospital (for patients in the ED), or remain in the hospital (for patients already in the hospital) as appropriate.

**Table 3 Tab3:** Flow of study procedures for patient participants

	**Study period**						
	**Enrollment**	**Allocation**	**Post-allocation**				
**Time point**	*** − T***_***1***_	**0**	***T***_***1***_	***T***_***2***_	***T***_***3***_	***T***_***4***_	***T***_***5***_
**Enrollment**							
Eligibility screen	X						
Informed consent	X						
Allocation		X					
**Interventions**							
CACP care			X				
**Assessments**^**a**^							
Age, sex, race, ethnicity, comorbidities, medications (EHR)	X						
Social support information (survey)		X					
HRQoL—EQ-5D (survey)		X			X		
Treatment burden—PETS (survey)		X			X		
ED visits, unplanned hospitalizations, death (EHR)					X	X	X
Falls with injury, medication errors with harm					X		
Program experience (survey and interview^b^)				X			

* − T*_*1*_ enrollment, *0* allocation, *T*_*1*_ first CP visit, *T*_*2*_ after last CP visit (note: *T*_2_ can be before or after *T*_3_, depending on the patient’s clinical need and how long they will be receiving CP services), *T*_*3*_ 30 days post-allocation, *T*_*4*_ 6 months post-allocation, *T*_*5*_ 12 months post-allocation

^a^Assessments are interviews, self-report surveys, and EHR (chart abstraction)

^b^Patients in the CACP program will complete a *T*_2_ survey. A sample of patients in the CACP program will be recruited to participate in an interview

Patient participants will be followed for 1 year post-allocation. They will complete surveys at baseline and 30 days; participants randomized to CACP will also complete surveys after their last CP visit. The EHR will be used to ascertain ED visits and unplanned hospitalizations (e.g., excluding planned hospital admissions for scheduled surgeries, procedures, and/or treatments at 30 days, 6 months, and 12 months post-allocation). If patients received CP services as part of usual care between 30 days and 12 months, this will be identified from the EHR and accounted for in the analyses.

#### Sample size {14}

For aim 1, the sample size will be assessed iteratively during data collection and analysis with the aim of ensuring that the implementation plan is feasible and meets the needs of key user groups. We anticipate up to 25 interviews in the pre-implementation phase for aim 1.

The aim 2 sample size was calculated on the basis of the primary hypothesis. Pilot studies of CP care on days out of ED or hospital in the first 30 days yielded an estimated mean of 27 days in the intervention group. A difference of 2 days was considered clinically important by stakeholders. We have powered this trial to detect a 10% improvement in the primary outcome. To detect a mean difference of 2 days out of ED or hospital at 30 days with a two-sided significance level of 0.05 and a power of 80% with equal allocation to two arms would require 120 patients per group assuming a pooled standard deviation of 5 days. The standard deviation was estimated by assuming the range of measurement will span approximately six standard deviations. Because the primary endpoint is assessed at 30 days and based on the coverage of the EHR, we expect minimal drop-out and missing data. Multiple imputation will be used if more than 20% of patients have missing data on the primary outcome. Aim 3 qualitative inquiry will use a purposeful sampling approach to intentionally select participants who can provide information about their experiences with the program. Based on the past experience of this team, the heterogeneity of expected patient situations, and the scope of this inquiry, we anticipate conducting approximately 25 patient interviews. We anticipate up to 35 clinicians and other stakeholders will also complete aim 3 interviews.

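### The sample-size figures do not follow from their own inputs: 2 days at SD 5 with 80% power needs 100 per group, not 120, and 2 days is about 8%, not 10%; both slips are conservative, and the SD has a weak basis

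*Protocol article*

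**What the plan says.** All the relevant statements are in one paragraph of the protocol article, Sample size {14}.

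- **Target.** Stakeholders considered a 2-day difference clinically important, and pilot studies gave an estimated mean of 27 days in the intervention group. The paragraph then says: "We have powered this trial to detect a 10% improvement in the primary outcome".
- **Calculation.** It begins "To detect a mean difference of 2 days out of ED or hospital at 30 days", specifies a two-sided significance level of 0.05 and "a power of 80% with equal allocation to two arms", and concludes that this "would require 120 patients per group assuming a pooled standard deviation of 5 days".
- **Source of the SD.** "The standard deviation was estimated by assuming the range of measurement will span approximately six standard deviations".
- **Losses.** "we expect minimal drop-out and missing data". No inflation factor is given. The 20% mentioned next is only the level of missing primary-outcome data above which multiple imputation would be used.

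The primary outcome counts days within a 30-day window (Trial design {8}), so it cannot exceed 30. The primary test is a two-sample t test, with a rank-based fallback if skew or kurtosis checks fail (Statistical methods {20a}, Aim 2).

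**The concern.** The paragraph presents a finished calculation, so a reader should be able to repeat it. Three things get in the way.

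1. The stated inputs do not lead to 120 per group.
2. The absolute target (2 days) and the relative target (10%) are given as the same thing, but with an intervention mean of 27 they are not.
3. The SD, the input to which power is most sensitive, comes from a range rule suited to a roughly symmetric variable centred in its range. Here the expected mean lies 3 days below the ceiling.

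At stake is how the result will be read. Anyone interpreting a null or borderline finding needs to know which difference, SD and allowance for loss the trial was built on. As written, 80% power, 120 per group and SD 5 cannot all hold together for 2 days.

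**Working it through.** **Inputs, all from Sample size {14}:** difference 2 days; SD 5; two-sided alpha 0.05; power 80%; allocation 1:1; intervention mean 27; no stated inflation.

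**1. Attempt to reproduce 120 per group**

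Normal approximation, with z values 1.960 and 0.8416:

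n = 2 × (1.960 + 0.8416)² × (5/2)² = 2 × 7.849 × 6.25 = 98.1, so 99 per group.

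Noncentral t, standardised difference 2/5 = 0.4: n = 99.08, so 100 per group (power 79.97% at 99 and 80.4% at 100).

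The stated 120 is not reproduced; it is 20% above 100. Other conventions do not reach it either:

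| Variant | n per group |
|---|---|
| One-sided, 80% | 78 |
| One-sided, 90% | 108 |
| Two-sided, 85% (t) | 114 |
| Two-sided, 90% (t) | 133 |
| Rank-sum test, efficiency 3/π | 104 |
| Rank-sum test, worst-case efficiency 0.864 | 115 |
| SD = 31/6 | 105 |

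120 does appear with inputs the article does not state: 100 × 1.20 = 120, 99/(1 − 0.17) = 120 after rounding up, or an SD of about 5.5.

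**2. Power that 120 per group gives on the stated inputs**

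2 / (5 × √(2/120)) = 2/0.6455 = 3.098, and 3.098 − 1.960 = 1.138. The normal approximation gives 87.3%; the t test gives 87.0%.

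**3. Is 2 days a 10% improvement?**

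- Implied control mean: 27 − 2 = 25 (derived, not stated).
- 2/25 = 8.0%; relative to the intervention mean, 2/27 = 7.4%.
- 2 days is 10% only of 20 days, a figure the paragraph does not contain.
- 10% of 25 is 2.5 days: t gives n = 63.8, so 64 per group.
- If 27 is 10% above control, control is 27/1.1 = 24.55 and the difference is 2.45 days: t gives n = 66.1, so 67 per group.

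**4. The SD**

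30/6 = 5. At mean 27 the ceiling is (30 − 27)/5 = 0.6 SD above the mean; a normal distribution with that mean and SD would put 27% of patients above 30. The near-normal picture behind the rule therefore does not fit. That does not rule out an SD of 5: the largest SD possible on 0 to 30 with mean 27 is √(27 × 3) = 9.0.

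Power of the t test for 2 days at 120 per group:

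| SD (days) | 4 | 5 | 5.5 | 6 | 7 | 8 |
|---|---|---|---|---|---|---|
| Power | 97% | 87% | 80% | 73% | 60% | 49% |

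Power stays at 80% or more up to an SD of about 5.5.

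**The case against.** The strongest reply is that nothing here harms the trial. On its own inputs, 120 per group delivers more power than claimed, and a trial sized for 2 days is more than large enough for 2.5. The 2-day target is also clear: it is the difference stakeholders chose and the one used in the calculation, so the 10% reads as a loose gloss. A 20% allowance may simply have gone unmentioned. All of this stands, except that an unmentioned allowance cannot be read into the text. The article attributes 120 to the listed inputs and expects minimal loss.

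On the SD, the article openly presents the six-SD rule as an approximation, and the analysis section has checks and a fallback for non-normality. Skew at a fixed SD matters little. In an illustrative simulation with scaled beta distributions on 0 to 30, means 27 and 25 and SD 5 in both arms (skew about −2.3 at mean 27, an assumed shape), the t test with 120 per group had 86% power. So the open question is the size of the SD, not the ceiling as such.

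A reader might go further and infer that the trial is under-powered or that an SD of 5 is wrong. The documents do not support either. They give no observed SD, 5 is within the feasible range, and smaller values are no more excluded than larger ones. Nor is 20% a planned loss; it is only the trigger for imputation.

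**Conclusion.** The point holds as a reporting error in the design figures, together with a weakly supported assumption.

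- **Sample size.** The stated inputs need 100 per group by t, not 120. Equivalently, power at 120 is about 87%, not 80%. This is arithmetic on stated inputs and needs no assumption.
- **Relative effect.** 2 days is about 8%, not 10%. This rests on an implied control mean of 25.
- **Direction.** Both slips are conservative, and neither shows under-powering.
- **SD.** One sixth of the range is a weak basis for an outcome with mean 27 and ceiling 30. Whether 120 per group is ample or short depends on an SD the documents do not report: about 5.5 is the break-even for 80% power on 2 days, assuming a t test, equal SDs and complete outcome data.

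**What to change.** Reword the paragraph, with no change in enrolment.

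1. State that 100 per group gives 80% power, and 120 per group about 87%, for a difference of 2 days (25 versus 27, about 8%) at SD 5 and two-sided alpha 0.05. Alternatively, keep 80% and state the inflation that takes 100 to 120, with its reason.
2. Replace the 10% improvement with 2 days (about 8%).
3. Base the SD on pilot data if a usable figure exists; the article reports only a pilot mean. Otherwise keep 5 as an assumption and show power at 120 per group over SDs on both sides of it, as in the table above.

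The cost is a few sentences. The one downside is that the stated power may become less favourable if the SD exceeds about 5.5.
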